## Abstract

**Background:**

Experience and development of pain may be influenced by a number of physiological, psychological, and psychosocial factors. In a previous study we found differences in neuronal activation to noxious stimulation, and microstructural neuroanatomical differences, when comparing healthy volunteers with differences in size of the area of secondary hyperalgesia following a standardized burn injury.

**Objective:**

We aim to investigate the degree of association between the volume of pain-relevant structures in the brain and the size of the area of secondary hyperalgesia following brief thermal sensitization.

**Methods:**

The study consists of one experimental day, in which whole-brain magnetic resonance imaging (MRI) scans will be conducted including T1-weighed three-dimensional anatomy scan, diffusion tensor imaging, and resting state functional MRI. Before the experimental day, all included participants will undergo experimental pain testing in a parallel study (Clinicaltrials.gov Identifier: NCT02527395). Results from this experimental pain testing, as well as the size of the area of secondary hyperalgesia from the included participants, will be extracted from this parallel study.

**Results:**

The association between the volume of pain-relevant structures in the brain and the area of secondary hyperalgesia will be investigated by linear regression of the estimated best linear unbiased predictors on the individual volumes of the pain relevant brain structures.

**Conclusions:**

We plan to investigate the association between experimental pain testing parameters and the volume, connectivity, and resting state activity of pain-relevant structures in the brain. These results may improve our knowledge of the mechanisms responsible for the development of acute and chronic pain.

**ClinicalTrial:**

Danish Research Ethics Committee (identifier: H-15010473). Danish Data Protection Agency (identifier: RH-2015-149). Clinicaltrials.gov NCT02567318; http://clinicaltrials.gov/ct2/show/NCT02567318 (Archived by WebCite at http://www.webcitation.org/6i4OtP0Oi)

## Introduction

The experience and development of pain may be influenced by a number of physiological, psychological, and psychosocial factors. However, our knowledge of the mechanisms responsible for acute and chronic pain is still not complete. A standardized burn injury in the skin provokes reversible primary and secondary hyperalgesia in healthy volunteers. Injury-induced primary hyperalgesia is located in the traumatized area and is characterized by reduced thresholds for thermal and mechanical stimulation. Secondary hyperalgesia is located around the traumatized area, and is characterized by reduced thresholds for mechanical stimulation [1,2].

Previous studies have demonstrated that secondary hyperalgesia to punctate mechanical stimuli is a result of changes in the central nervous system, in part due to sensitization in response to nerve signals by A-fiber nociceptors [1,3-5]. Secondary hyperalgesia can be provoked by a number of different conditioning stimuli, and according to previous studies this is a robust phenomenon that can be applied to investigate basic pain physiology [2,6,7]. Central neuronal sensitization is presumed to play an important role in a number of different pain conditions, such as osteoarthritis, fibromyalgia, and postoperative pain [3].

To investigate the basic physiological mechanisms of pain, our research group has worked extensively with experimental physiological pain models [8-10]. In previous studies, we found indications of large inter-individual variations in the size of the area of secondary hyperalgesia following identical experimental pain stimulation. Moreover, we observed that the area of secondary hyperalgesia may be an identifiable phenotypic indicator and predictor of individual pain responses [10,11].

To further explore the pathophysiology of central sensitization, we first investigated functional changes in the brain by magnetic resonance imaging (MRI) after induction of secondary hyperalgesia by a first degree burn injury. The first degree burn injury was induced 100 minutes before initiation of MRI, and interestingly we found differences in neuronal activation to noxious stimulation in healthy volunteers that developed either large or small areas of secondary hyperalgesia. These findings suggest differences in central pain processing related to phenotypical expression of secondary hyperalgesia. Furthermore, we found indications of differences in the volumes of the caudate nuclei, as well as other microstructural neuroanatomical differences between the two groups [11], encouraging further studies with larger sample sizes to elucidate the importance of each finding in the pathophysiology of pain and central sensitization.

The basal ganglia have proved to be essential in the pain processing in humans [12-14]. Moreover, the role of the caudate nuclei in the processing and modulation of pain have been investigated in human [12-27] as well as animal [28-39] studies. The caudate nuclei are believed to play a role in integration and control of sensory, motor, and motivational information, and thus essential in coordinating behavioral responses [14]. The caudate nuclei have also been demonstrated to be involved in the sensory processing and spatial location of noxious stimuli [24], in the suppression and modulation of pain [26], and are activated during pain expectancy [40].

Reduced grey matter volume of the caudate nuclei has been demonstrated in patients with trigeminal neuralgia [20], knee osteoarthritis [22], lumbar disc herniation [21], and migraines [15,27]. Moreover, reduced regional cerebral blood flow in the caudate nuclei has been seen in patients with fibromyalgia [23], familial restless legs syndrome [25], and chronic fatigue syndrome [16]. Thus, the caudate nuclei are essential sites of pain processing, and may play a role in the development of secondary hyperalgesia, and consequently in the processes involved with central sensitization.

A recent study confirmed that areas of secondary hyperalgesia have a low intra-individual variation compared to the inter-individual variation [41]. This finding enables us to phenotype healthy volunteers based on the size of the area of secondary hyperalgesia. It remains uncertain whether these phenotypes are related to other pain syndromes or entities, are involved in the risk of developing chronic pain, or influence factors in the individual’s pain sensitivity. Likewise, it is unclear if important structures such as the caudate nuclei (or other CNS differences) are closely related to secondary hyperalgesia phenotyping, warranting more research in this area.

With this study we aim to investigate the association between the volume of pre-defined pain-relevant structures in the brain and the size of the areas of secondary hyperalgesia.

## Methods

### Study Design

This study is a confirmatory study designed to investigate the association between the size of the area of secondary hyperalgesia following brief thermal sensitization (BTS; see *Clinical Evaluations*) and the volume of the caudate nuclei in healthy volunteers. On the experimental day, a whole brain MRI scan will be conducted including T1-weighed three-dimensional (3D) anatomy scan, diffusion tensor imaging, and resting-state functional MRI (rs-fMRI), in consecutive sequence (see *Clinical Evaluations*). No other tests or assessments will be performed on the experimental day. The total duration of the experimental day is approximately 50 minutes.

Before the experimental day, all included participants will undergo pain testing in a parallel study (Clinicaltrials.gov Identifier: NCT02527395). Results from the pain testing, as well as the size of the area of secondary hyperalgesia from the included participants, will be extracted from this parallel study. The experimental day will be conducted at a maximum of 2 months and a minimum of 2 weeks after the completion of the BTS and additional pain testing.

### Setting

The MRI scans will be conducted at the Department of Radiology, Bispebjerg and Frederiksberg Hospitals, Copenhagen, Denmark. The data analysis will be conducted at the Department of Anesthesiology, Centre of Head and Orthopedics, Rigshospitalet, Copenhagen, Denmark.

### Study Participants

Healthy male volunteers will be included in the study. The study participants will receive information regarding possible risks and side effects, and will be provided with written and oral information concerning the study. The participants will receive €67 (US $74) for their participation in the study. Inclusion and exclusion criteria are presented in Table 1.

**Table table1:** Inclusion, and exclusion criteria.

Inclusion criteria	Exclusion criteria
Age ≥18 years and ≤35 years	Study participants who cannot cooperate to the test
Male sex	Study participants with a substance abuse, assessed by the investigator
Study participants who have a weekly intake of >21 units of alcohol, or a have consumed >3 units of alcohol within 24 hours before experimental day Speak and understand the Danish language Signed informed consent Have participated and completed the study: “*To determine the degree of association between Heat Pain Detection Threshold and area of secondary hyperalgesia following Brief Thermal Sensitization in healthy male volunteers”* (Clinicaltrials.gov Identifier: NCT02527395)	Study participants who have consumed analgesics within 3 days before experimental day Study participants who have consumed antihistamines within 48 hours before experimental day Study participants who have consumed antidepressant medication within 30 days before the study Study participants who have consumed prescription medicine within 30 days before the study Study participants with neurological illnesses Study participants with chronic pain
	Study participants with psychiatric diagnoses
	Study participants with eczema, wounds, or sunburns on the sites of stimulation
	Study participants with a Body Mass Index of >30 kg/m^2^ or <18 kg/m^2^
	Study participants with contraindications to MRI^a^
	Study participants that decline information regarding potential pathological findings in relation to the MRI
	Study participants that have any kind of trauma resulting in pain and administration of analgesics in the period between experimental pain testing and MRI scan
	Study participants that experience a head trauma in the period between the experimental pain testing and the MRI scan
	

^a^Contraindications to MRI includes: claustrophobia, pacemaker implant, artificial heart valve, cochlear/stapes prosthetics, irremovable insulin pump, neurostimulator, metal clips from previous surgical procedures, other metallic foreign objects, shrapnel or shell splinter, catheters (eg, Swan Ganz), shunts and drainage tubes, and surgical procedures within 6 weeks before the study (subjected to individual evaluation).

Before the experimental day, each participant will be tested with the experimental pain models: BTS, heat pain detection threshold (HPDT), and pain during 1 minute of thermal stimulation of the skin (p-TS), as well as two psychological tests: Pain Catastrophizing Scale (PCS) and Hospital Anxiety and Depression Score (HADS; see Multimedia Appendix 1 and Clinicaltrials.gov identifier: NCT02527395). The results will be blinded to the investigator evaluating the MRI scans. Prior to, as well as on the experimental day, the investigator will interview all participants, and those that have one or more psychiatric or neurological diagnoses or illnesses will be excluded. All participants with prior history of psychiatric or neurological illness will also be excluded.

### Clinical Evaluations

#### Pain Testing

BTS, HPDT and p-TS are not performed as a part of this study per se, but all participants in the present study have been tested using these methods in a parallel non-imaging study (Clinicaltrials.gov Identifier: NCT02527395). Data concerning secondary hyperalgesia from this concurrent study will be extrapolated and included in the present study. The BTS method is briefly explained below. For further details, please refer to Multimedia Appendix 1.

#### Brief Thermal Sensitization

A computer-controlled thermode (Somedic MSA Thermotester; size 2.5 x 5 cm) is placed on the participant’s skin, centrally on the anterior part of the right thigh. The initial temperature of the thermode is 32°C, and the temperature is increased 1°C/second until it reaches 45°C. The temperature of the thermode remains a constant 45°C for 3 minutes, and while the thermode still has contact with the skin, the assessment of secondary hyperalgesia is conducted. The assessment of secondary hyperalgesia takes approximately 1-2 minutes, with a maximum duration of heat stimulation of 5 minutes.

#### Assessment of Secondary Hyperalgesia

The area of secondary hyperalgesia is quantified after stimulation with a 19G monofilament (von Frey hair) in 4 linear paths arranged in 90° around the center of stimulation. Stimulation will begin 15 cm from the center of stimulation and advance in steps of 5 mm with 1 second intervals towards the center of stimulation. When the participant states a clear change in sensation (ie, intense pricking, burning, tenderness) the place will be marked with a felt pen and the transverse and longitudinal axes will be measured for later area calculation.

#### MRI Scans

The MRI scans will be performed with a Siemens MAGNETOM Verio 3-tesla, with b17 software, and a 32-channel head coil. The specific MRI sequence and settings are detailed in Multimedia Appendix 2.

#### Anatomical MRI Scans

T1-weighted images are recorded in order to construct detailed anatomical images of the brain. These images will be used to perform morphometry/volumetric analysis of cortical and subcortical structures in order to determine possible differences in the study population. To look for potentially confounding structural lesions and perfusion asymmetry, T2-weighted, T2-FLAIR, diffusion weighted imaging, gradient echo, and arterial spin labeling will also be performed as part of the imaging protocol (Figure 1).

**Figure 1 figure1:**
[figure not shown]
Schematic presentation of experimental day. Abbreviations: MRI, Magnetic Resonance Imaging; fMRI, Functional Magnetic Resonance Imaging.

#### Diffusion Tensor Imaging

Diffusion tensor imaging (DTI) is sensitive to the diffusion of water molecules. The net-diffusion of water molecules roughly occurs along the direction of the axons; hence, DTI can be utilized to perform white matter tractography (neuronal connections of the brain), or to detect changes in the white matter by using Tract-Based Spatial Statistics.

#### Resting State Imaging

In rs-fMRI the intrinsic connectivity networks of the brain are mapped by indirectly measuring so-called *spontaneous brain activity*. Rs-fMRI measures spontaneous changes in blood-oxygenation-level-dependent signal by detecting concomitant changes in magnetization that accompanies regional changes in brain blood flow.

#### Other Scans

As a supplement to the previously mentioned MRI scans, it is necessary to perform a number of technical MRI scans as well (ie, B0 field maps). These supplementary scans are necessary and important for later data analyses, and will not result in any further discomfort for the participants. For schematic presentation of the general procedure and the MRI scan sequence on the experimental day, please refer to Figure 1.

Participants will be informed that they must stay awake during the MRI scan period, and if they fall asleep they are obliged to inform the investigator. Participants that fall asleep during the MRI scan period will be excluded from the study.

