### Sample Size Estimation

Based on results from a previous study [11], sample size calculations are based on a Z-test of the Fisher transformed Pearson correlation. With a true correlation of r=-0.4 between the area of secondary hyperalgesia and the caudate nuclei, and a significance level of 2.5% to 5% according to the single step method (refer to *Statistical Significance*), a sample size of 52 is needed to obtain a power of 0.80 (β=0.20).

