### Statistical Analyses

#### Statistical Analysis of Primary Outcome

The estimates of the volumes, from the T1-weighted 3D anatomical scans of the caudate nuclei (mm^3^), will be exported to a spreadsheet for regression analysis to assess the association between volume of caudate nuclei and secondary hyperalgesia areas. The association of the volume of the left and right caudate nuclei and the area of secondary hyperalgesia will be investigated by linear regression of the estimated best linear unbiased predictors (EBLUPS) on the individual volumes of the left and right caudate nuclei. The ability of the volume of caudate nuclei to predict individual variation in the area of secondary hyperalgesia will be investigated by linear regression on the EBLUPS as a function of the individual volumes of the caudate nuclei.

Significance of the caudate nuclei as a predictor will be assessed by analysis of variance (ANOVA) methods and the predictive ability will be quantified by summary of prediction error, including 95% prediction interval for the prediction of the size of the area of secondary hyperalgesia. Relevant examples will be presented illustrating how accurately the volume of the caudate nuclei predicts the area of secondary hyperalgesia in the individual participants or vice versa. The association will be expressed in R^2^and prediction intervals for the area of secondary hyperalgesia given fixed values of the caudate nucleus’ volume. All analyses of structural MRI data (both in the primary, secondary, and exploratory outcomes) will be adjusted for age.

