### Missing Data

For all analyses, an intention-to-test analysis will be performed including all subjects that participated in the experimental day. Analyses will be based on all observed data. In case of missing data exceeding 5%, and indication of violation of *missing completely at random* by a statistically significant Littles test, a sensitivity analysis based on an appropriate model for *missing data at random* or *missing data not at random* will be performed.

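### Excluding participants who fall asleep from the whole study conflicts with the intention-to-test rule, leaves the primary analysis set undefined, and may needlessly discard usable T1 data

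*Protocol article*

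**What the plan says.** Two rules decide who is analysed.

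- **Other Scans** (Clinical Evaluations). Participants are told to stay awake, and "if they fall asleep they are obliged to inform the investigator". The consequence is unrestricted: "Participants that fall asleep during the MRI scan period will be excluded from the study". The sentence names no particular sequence or outcome.
- **Missing Data.** "For all analyses, an intention-to-test analysis will be performed including all subjects that participated in the experimental day". The next sentence adds: "Analyses will be based on all observed data". No exception for sleep is given.

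Three other sections bear on how the two rules meet.

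- **Study Design** lists the T1 anatomy scan, diffusion tensor imaging and resting-state fMRI as one consecutive session, and adds: "No other tests or assessments will be performed on the experimental day".
- **Statistical Analysis of Primary Outcome** takes its volumes from the anatomical scan alone: "The estimates of the volumes, from the T1-weighted 3D anatomical scans of the caudate nuclei (mm^3^), will be exported to a spreadsheet for regression analysis".
- **Sample Size Estimation** states that "a sample size of 52 is needed to obtain a power of 0.80", for a true correlation of -0.4 and a significance level between 2.5% and 5%. It mentions no allowance for exclusions.

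**The concern.** A participant who dozes off during the session has taken part in the experimental day. One rule removes that person from everything; the other keeps that person in every analysis. An analyst cannot follow both, and the primary test of left and right caudate volume against hyperalgesia area is among the analyses affected.

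The whole-study scope also looks wider than its evident purpose. Wakefulness plainly matters for a scan of spontaneous brain activity, but that scan feeds only an exploratory outcome. Applied to the whole study, the rule can remove T1 and diffusion data that may be perfectly usable. The only trigger the article describes is the participant's own report. The Ethics section mentions monitoring equipment in the scanner but does not link it to detecting sleep.

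What is at stake is a primary analysis set fixed in advance, together with some power.

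**Working it through.** **Step 1. The two rules applied to one person.** Take a participant who completes the session and reports having slept during part of it.

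| Section | Criterion | Result |
|---|---|---|
| Other Scans | Fell asleep during scanning | Out of the study |
| Missing Data | Participated in the experimental day | In all analyses, with all observed data |

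Study Design makes the MRI session the whole experimental day, so the second criterion is met. The instructions are opposite.

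**Step 2. Which outcomes depend on wakefulness, by the article's own account.**

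| Scan | What the article says it captures | Where it is used |
|---|---|---|
| T1 | Brain anatomy, for volumetry (Anatomical MRI Scans) | Primary outcome; regional volumes in the secondary and exploratory outcomes |
| Diffusion | Diffusion of water molecules (Diffusion Tensor Imaging) | Secondary outcome 2; exploratory 5b and 5c |
| Resting-state fMRI | Spontaneous brain activity (Resting State Imaging) | Exploratory outcome 6 |

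Nothing in the article says that sleep spoils a T1 volume or a diffusion measure. That such data remain usable is an inference from these descriptions, not something the article states.

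**Step 3. Reproduce the sample size.** Inputs from Sample Size Estimation: r = -0.4, power 0.80, alpha 2.5% to 5%, Z-test on the Fisher-transformed correlation. Sidedness is not stated; I take two-sided.

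n = ((z for 1-alpha/2 + z for power) / atanh(0.4))² + 3, with atanh(0.4) = 0.4236 and z for power = 0.8416.

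- alpha 0.05: ((1.960 + 0.8416)/0.4236)² + 3 = 46.7, so 47.
- alpha 0.025: ((2.241 + 0.8416)/0.4236)² + 3 = 56.0, so 56.
- n = 52 with power 0.80 corresponds to alpha 0.0337, inside the stated range. Under the single-step method this lies between correlations of 0.85 and 0.90 for the two test statistics (n = 52.3 and 51.5). The article does not give that correlation.

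So 52 is consistent with the stated inputs.

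**Step 4. Power if participants who sleep are lost.** Power = Phi(0.4236 × sqrt(n - 3) - z for 1-alpha/2). Assumptions: 52 are scanned, none is replaced, and the sleep rate is 5%, 10% or 15%. The article gives no rate.

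| Assumed loss | n | alpha 0.05 | alpha 0.0337 | alpha 0.025 |
|---|---|---|---|---|
| 0% | 52 | 0.843 | 0.800 | 0.766 |
| 5% | 49 | 0.819 | 0.773 | 0.736 |
| 10% | 47 | 0.802 | 0.754 | 0.715 |
| 15% | 44 | 0.774 | 0.722 | 0.681 |

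Each column must be read from its own first row. At alpha 0.025, for instance, the losses due to sleep are 0.030, 0.051 and 0.085. The gap between 0.800 and 0.766 comes from the stricter level, not from sleep.

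**The case against.** **The specific rule may override the general one.** Someone excluded from the study is arguably no longer a subject to whom the Missing Data section applies. This does not remove the conflict: that section defines its set by participation in the experimental day, covers all analyses and names no exception. It does show that the documents do not force one particular remedy. Sleep could instead be written in as a stated exception, with a sensitivity analysis that includes these participants.

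**The 52 may be evaluable participants.** The article does not say whether 52 is the number scanned or the number analysed, nor whether excluded participants are replaced. If they are replaced, power stays at 0.80. This stands, and the power figures are therefore conditional. A reader might infer that the study is bound to fall short of 0.80; the documents do not support that.

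**Validity of the T1 and diffusion data is not proven.** The article does not say whether scanning continues after sleep or whether image quality suffers, and the scan schematic is not shown. This also stands. Any structural data kept should first pass their own quality check.

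**A reader might infer bias in the primary result.** The documents show none. The exclusion is stated in advance, the pain results are blinded to the investigator evaluating the scans, and hyperalgesia area is blinded until the T1 analysis is complete. Nothing links falling asleep to the association between caudate volume and area.

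**A reader might also suppose that the resting-state head-movement limits remove people from the structural analyses.** They do not: the article states them only as quality assurance for resting-state fMRI.

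**Conclusion.** The concern holds as a contradiction between two current rules that leaves the primary analysis set undefined for anyone who falls asleep. It also holds that a whole-study exclusion can needlessly discard usable primary data, given that the article offers no reason why sleep would affect them.

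The size is uncertain. The number affected is unknown and could be zero. If 52 are scanned and none replaced, assumed losses of 5% to 15% cost about 0.03 to 0.08 of power at alpha 0.0337 and about 0.03 to 0.09 at 0.025. At alpha 0.05, power is still 0.80 after a 10% loss.

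Severity is moderate. The main harm is the undefined analysis set; the power loss is secondary and conditional.

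**What to change.** 1. **Other Scans:** limit the sleep exclusion to the resting-state fMRI analysis (exploratory outcome 6). Keep participants who fell asleep in the T1 and diffusion analyses when those images pass their own quality check.
2. **Missing Data:** state that a sleep exclusion from resting-state fMRI does not remove a participant from the other analyses.

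Settle both before the hyperalgesia areas are unblinded, so that the primary set is not chosen with results in view.

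The cost is one sentence in each of two sections and no new data. The analysis sets will differ slightly between modalities. That is easy to report, because the Ethics section already places the primary and secondary outcomes in one publication and exploratory outcomes 5 and 6 in another.
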